##### Objective 1.2: Feasibility of the Intervention

This objective will mainly be investigated through the qualitative data analyses reported in the next section. Simple quantitative analyses will be conducted to examine the relevance of our motivational and educational messages (ie, scores provided to the text messages at the individual and collective levels). We also report the percentage of missing values for each measurement burst.

##### Objective 2.1: Identifying Potential Mechanisms of Action Mediating the Effect of the Intervention on Eating Behaviors

Longitudinal mediation analyses will be conducted to understand the processes through which the intervention will potentially affect the environmental sustainability of eating behaviors. These analyses will be conducted independently for the 7 potential mediators presented in the section *Mechanisms of Action* (ie, motives for health, environmental, social, and affordability; ecoanxiety; habits; and self-efficacy) and by following recent guidelines based on longitudinal multilevel structural equation models [51]. These analyses will be performed for the total sample and per socioeconomic subgroup with the environmentally sustainable healthy diet index as the first dependent variable and, in secondary analyses, with the weekly level of the relevant food outcomes mentioned in objective 1.1.b (ie, red and processed meat, fruits and vegetables, ultraprocessed food, dairy products, and food waste). These food groups and food waste will be analyzed here at the weekly level to match the temporal resolution of the mechanisms of action that are also assessed weekly (and not daily).

##### Objective 2.2: Identifying Potential Covariations and Spillover Effects Among Food Groups and Between Food Composition and Food Waste

Covariations and spillover effects will be examined using network visualizations of the partial correlation matrix by following published guidelines and previous applications in the health behavior domain [52,53]. The within-participant network will be computed by subtracting the mean of each participant’s behavior across the 15 assessment weeks from their scores at each time, thus estimating a network of interrelationships centered on each person’s “average” behavioral pattern over 12 months. This method allowed us to test whether variations from the mean level for one behavior are associated with variations from the mean for other behaviors and, hence, covariation or spillovers. These networks will be estimated for the total group and the 3 socioeconomic subgroups using the 12 items presented in Table 2. Data from the 3 phases will be combined together to maximize the statistical power.

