### Prior Work

Recently, some interventions have been designed with the aim of promoting individual eating behavior change considering different dietary sustainability dimensions. For instance, O’Sullivan et al [12] have designed an intervention to encourage the adherence to a healthy diet with low environmental impact, but they have left aside other relevant behaviors to achieve a sustainable diet, such as food waste, and the socioeconomic consequences of dietary behaviors. An intervention implemented by Monroe et al [13] among US students has targeted food waste reduction and considered the social dimension of individual eating behaviors, such as promotion of the acquisition of local foods from farmers’ market. However, this intervention has not tackled the overall dietary pattern of the participants, focusing only on red meat consumption as the main outcome. Besides considering red meat reduction is key to transitioning to sustainable healthy diets, this approach lacks an assessment of the substitution effect and possibility of other changes in untargeted food groups (ie, spillovers), which could offset the overall effect of the intervention [14]. For example, if pork meat is replaced by hard cheese (one of the food products with the highest environmental impact), the dietary environmental impact would increase [15]. Therefore, eating behavior change interventions aimed at promoting sustainable healthy diets as a whole, that is, as a complex interplay of behaviors, are needed [16].

Beyond interventional studies, reviews have documented potential mechanisms of action that motivate or impede behavior change for a healthy and sustainable diet. A diversity of personal and interpersonal factors have been highlighted, such as sociodemographic determinants (ie, gender, age, socioeconomic level, and political orientation), food-related factors (ie, healthiness, taste, and affordability), generic motivational factors (ie, self-efficacy and habit), and specific motives for sustainability (ie, environmental impact, ecoanxiety, and social justice) [17-21]. By contrast, specific barriers have been identified, such as perceiving sustainable healthy food as less tasty [19]. These previous findings are useful for designing interventions (as levers to manipulate and be considered during a study) and for understanding the mechanisms of action that potentially mediate the effect of an intervention on behavior change.

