##### Eating Behavior Scoring Procedure

In terms of the scoring procedure, we designed an index for assessing dietary healthiness and environmental sustainability for every assessment week based on 10 out of the 12 items provided in Table 1. The item related to white meat, eggs, and fish is not considered in the score to avoid overrating protein groups. However, it will be used in the individual food analysis to assess whether, in the case of a reduction in the consumption of red and processed meat and not a simultaneous increase in legume consumption, red and processed meat is replaced by animal-based proteins (objective 2.2). The second item not included in the present index is the one assessing food waste. This last item will be used as a specific outcome in itself and is not included in our main score.

Therefore, the environmentally sustainable healthy diet score is computed from 10 items, each of which is treated continuously from 0 to 1 point; for example, the scoring of red and processed meat consumption is as follows: 0 points for the consumption of >2 servings of red and processed meat and 0.25, 0.5, 0.75, and 1 points for the consumption of 1.5, 1, 0.5, and 0 servings per week, respectively. Food consumption will be assessed as the average daily food consumed during the entire assessment week. The scoring criteria and rationales are listed in Table 3. The total score of the environmentally sustainable healthy diet index will be the sum of the points for each item. Thus, the environmentally sustainable healthy diet index will range from 0 to 10 points, with 0 points being the lowest score in terms of environmentally sustainable healthy diet and 10 points being the highest (best) score (Table 3). Our overall scoring criteria are based on the recommendations of reference entities in the field of nutrition, mainly the EAT-Lancet Commission, Food and Agriculture Organization, and World Health Organization [25,40,41].

**Table 3 table3:** Environmentally sustainable healthy diet index: scoring criteria.

Item	What does it assess?	Scoring criteria^a^	Rationale
Red and processed meat	Average daily red and processed meat consumption	1 point: 0 serv/w^b^ (or <0.15 serv/d^c^) 0 point: >2 serv/w (or >0.29 serv/d)	Ideally, no red or processed meat should be consumed in a sustainable healthy diet; however, up to 2 servings of red meat per week is acceptable [25].

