### Conclusions

This study will address the urgent topic of adopting overall sustainable healthy diets, thus filling a gap in the literature and providing pilot data for scaling up the intervention in a full randomized controlled trial. It will provide insights into the effectiveness of the pilot intervention in changing eating behaviors toward a sustainable healthy diet, considering the whole dietary pattern and, hence, spillovers among food groups and among dietary outcomes; it will help to determine the moderation and interaction effects of several individual characteristics, such as socioeconomic level and gender; and it will address its own feasibility to determine the barriers to and enhancers of the intervention, which will help us refine and optimize the intervention for future studies.

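### Objective 2.2 reads the edges of a phase-pooled, same-time network as spillover, but those edges mix ordinary fluctuation with change after baseline, and the food-level change analysis that could answer the substitution question is not specified

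*Protocol article*

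**What the plan says.** The protocol article poses a question about change.

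- Prior Work faults earlier studies for not assessing substitution and "changes in untargeted food groups (ie, spillovers), which could offset the overall effect of the intervention". The objectives that close that section place spillovers over the course of the study.
- Eating Behavior Scoring Procedure gives objective 2.2 a conditional question: if red meat falls and legumes do not rise at the same time, is it the case that "red and processed meat is replaced by animal-based proteins (objective 2.2"? It says the white meat, fish and eggs item will be used for this in an analysis of individual foods.
- Conclusions promises insight "considering the whole dietary pattern and, hence, spillovers among food groups and among dietary outcomes".

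The analysis section for objective 2.2 describes one method: "Covariations and spillover effects will be examined using network visualizations of the partial correlation matrix". Scores are centred by "subtracting the mean of each participant’s behavior across the 15 assessment weeks from their scores at each time", all 12 items of Table 2 are entered, and "Data from the 3 phases will be combined together to maximize the statistical power". The article says that centring in this way "allowed us to test whether variations from the mean level for one behavior are associated with variations from the mean for other behaviors". No lag, direction, phase term or baseline-only network is described. An edge is taken to show "variations from the mean for other behaviors and, hence, covariation or spillovers".

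The phase-based mixed models sit under objective 1.1.b. Their list names red and processed meat, fruits and vegetables, ultraprocessed foods, dairy and food waste. Neither white meat, fish and eggs nor legumes appears.

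**The concern.** Covariation follows from associated deviations; spillover does not. Phase is not in the network, so a week with more chicken and less beef counts the same whether it is ordinary variety during baseline or a lasting shift after the intervention began. A negative edge between red meat and white meat, fish and eggs could be reported as replacement when neither mean moved. A moderate real swap could look almost the same as no swap, or point to the wrong food.

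The practical stake is the offset that Prior Work warns about. Replacing red meat with legumes and replacing it with other animal protein are different results for this intervention. The change in means that would tell them apart is not assigned to any specified model.

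**Working it through.** **Figures in the article.** The counts reproduce: 21 × 15 = 315 weekly and 21 × 105 = 2205 daily observations, with 7 × 15 = 105 weekly observations per socioeconomic group. No edge size, threshold or power is stated for objective 2.2; the power simulation covers objective 1.1.a only.

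**Assumed inputs (not in the article).** Two main meals a day, so 14 protein slots a week. Slots are filled by red, white, legume or other at 0.30, 0.35, 0.15 and 0.20. The nine other items are independent. From week 3 a fixed share of red meat moves to one destination, equally in everyone, with complete data.

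**Step 1: what a pooled edge contains.** Treat the 2 baseline weeks and the 13 later weeks as two levels. After centring on the 15-week mean,

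pooled covariance(j,k) = average within-phase covariance + (2/15)(13/15) × Δj × Δk,

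where Δ is the change in weekly mean and (2/15)(13/15) = 26/225 = 0.116. Only the second term is about change.

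**Step 2: no change.** For alternating slots the partial correlation is −√[pR·pW / ((pR+pO)(pW+pO))].

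- Red-white: −√[0.30×0.35 / (0.50×0.55)] = −√(0.105/0.275) = −0.62
- Red-legume: −√[0.30×0.15 / (0.50×0.35)] = −√(0.045/0.175) = −0.51

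Simulation of the article's method gave −0.61 and −0.50, both significant in 100% of runs.

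**Step 3: 30% of red meat moves to white.** Red meat starts at 14 × 0.30 = 4.2 servings/week, so Δ = ∓1.26.

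- Change term: 0.116 × (−1.26)(1.26) = −0.18
- Within-phase term: (2/15)(−14×0.30×0.35) + (13/15)(−14×0.21×0.44) = −0.196 − 1.121 = −1.32

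The change term is 0.18/1.50, or about 12% of the pooled covariance. The rest is alternation.

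**Step 4: simulated weekly edges (SD about 0.04 to 0.05).**

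| Scenario | Red-white | Red-legume |
|---|---|---|
| No change | −0.61 | −0.50 |
| 30% to white | −0.63 | −0.48 |
| 30% to legumes | −0.59 | −0.58 |
| 60% to white | −0.67 | −0.46 |
| 60% to legumes | −0.56 | −0.65 |
| 60% to neither | −0.31 | −0.24 |
| 90% to white | −0.73 | −0.45 |
| 90% to legumes | −0.54 | −0.74 |

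With 30% moved to legumes, red-white was still the stronger edge in 59% of weekly and 99% of daily analyses. With equal starting shares (0.25 each) those figures were 18% and 4%. The ranking of edges therefore depends on the starting mix, which a pooled network does not show.

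**Step 5: weaker alternation.** In a separate simulation (undiluted no-change edge −0.66), independent servings at 0.5, 1 and 2 times the meal servings cut the no-change red-white edge to −0.34, −0.23 and −0.13. At equal servings, moving about 1.7 servings/week gave −0.23 (to white) and −0.18 (to legumes), SD about 0.05 to 0.06. With fully independent items the no-change edge is about 0. A 60% shift then shows on the correct edge (−0.18 to white, −0.22 to legumes). A 30% shift is mostly missed: −0.04, significant in 11% of runs (white), and −0.06, significant in 18% (legumes).

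**Step 6: change in means on the same simulated data (alternating meals).** Testing intervention-onward minus baseline across 21 people flagged each item in 3 to 6% of runs with no change. At a 30% shift it found the correct substitute alone in 90 to 93% (white) and 93 to 96% (legumes), and named the wrong one in about 0%.

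**The case against.** Four points deserve weight.

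1. Red meat, white meat, fish and eggs, and legumes are separate nodes. A reader might infer that the network can never tell a swap to white meat from a swap to legumes. That is not supported: at a 90% shift the correct substitute had the stronger edge in 100% of runs, and in 96 to 100% with independent servings added. This stands; the weakness is with moderate shifts and the missing baseline reference.
2. A reader might infer that the network is the only analysis planned. The scoring section names a food-level analysis for replacement, and the objective 1.1.b list may not be exhaustive. This also stands, so the point is that no section specifies that analysis for the two items it needs.
3. Alternation of main proteins is plausible, but the article does not say it, and Table 2 allows from 0 to more than 5 servings of each item per day. The size of the no-change edge rests on this assumption.
4. The objective is secondary, the Discussion gives no specific hypotheses for it, and the study is a pilot. Covariation is part of the objective, and the network suits that part.

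The last point excuses wide intervals. It does not excuse a stated inference from same-time association to spillover, which the article makes itself rather than leaving to a fuller plan.

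**Conclusion.** The concern holds in a limited form. A pooled, undirected edge mixes fluctuation with change whatever people eat, so it cannot by itself be read as spillover. How badly it misleads depends on the assumed alternation: a no-change red-white edge of about −0.6 when undiluted, about −0.2 at equal dilution, and about 0 without alternation. For shifts of about 30% of red meat the network does not reliably show whether substitution occurred or which food took over. For large shifts, or where alternation is weak, the red-white and red-legume edges do separate, though with no baseline edge to judge them against. The advantage of mean changes was shown for a uniform step change without missing data and would be smaller in practice. The primary index analysis is unaffected; this should be put right before objective 2.2 is analysed.

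**What to change.** Reconcile Eating Behavior Scoring Procedure, objective 1.1.b and objective 2.2:

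- Keep the network as a description of covariation, and remove spillovers as a reading of its edges.
- Add white meat, fish and eggs, and legumes, to the phase-based models of objective 1.1.b.
- For objective 2.2, report each participant's and the group's change from baseline, for intervention and for follow-up, in red and processed meat, white meat/fish/eggs, legumes, dairy and food waste. Give participant-level bootstrap intervals for the group changes.
- Give servings gained per serving of red meat lost only as a group-level descriptive figure, because the ratio is unstable when red meat changes little.

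The cost is a few sentences and one extra table from data already collected. Intervals from 21 people with 2 baseline weeks will be wider than the network appears to offer. Without a control group the results remain before-after changes.

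### The pooled spillover network (objective 2.2) cannot separate a common response to the intervention from spillover; a phase-centred network should be reported beside it

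*Protocol article*

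**What the plan says.** The section on objective 2.2 examines covariation and spillover through "network visualizations of the partial correlation matrix", estimated for the whole sample and for each socioeconomic group "using the 12 items presented in Table 2". The within-participant network is obtained by "subtracting the mean of each participant’s behavior across the 15 assessment weeks from their scores at each time". The reference point is therefore one yearly average per person and item. The phases are not separated: "Data from the 3 phases will be combined together to maximize the statistical power". No phase term, detrending or phase-specific network is mentioned. The section then says what an edge means: it shows whether "variations from the mean level for one behavior are associated with variations from the mean for other behaviors and, hence, covariation or spillovers".

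Three other places bear on this.
- The Prior Work section uses the word spillover for changes in food groups that an intervention did not target.
- The definition of a sustainable healthy diet under objective 1.1 shows that the intervention encourages fruit, vegetables, legumes, nuts and whole grains. It discourages meat, dairy, sugary, salty and ultraprocessed foods, and waste.
- Principal Findings expects meat, dairy and ultraprocessed food to fall and plant foods to rise.

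**The concern.** Subtracting a 12-month mean removes stable differences between people. It does not remove the movement from baseline to intervention to follow-up, which the intervention is designed to cause in many items together. Phase is then a common cause of several nodes. A partial correlation conditions on the other items but not on phase, so it does not take this out.

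Two targeted items that each respond directly to the messages and feedback, with no link between them, can therefore be joined by an edge. By the article's own use of the word, that is not spillover. Red meat and legumes show the problem. The scoring section says objective 2.2 will look at what replaces red meat when legumes do not rise. If meat falls and legumes rise, each for its own reason, the pooled network tends to show a negative edge that looks like substitution. What is at stake is the interpretation of a secondary objective whose results are to inform a later trial.

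**Working it through.** **Inputs from the article.** There are 21 participants (7 per socioeconomic group), 15 assessment weeks, 105 daily assessments and 12 nodes. The article's counts reproduce: 21 × 15 = 315 weekly rows, 7 × 15 = 105 per group, and 21 × 105 = 2205 daily rows. It gives no power or error rate for the network.

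**Assumptions.**
- Weeks per phase are 2 / 7 / 6. This is inferred from a 2-week baseline, assessments every 3 weeks over 22 weeks, monthly assessments over 6 months, and the total of 15.
- Item SDs are not given, so a shift d is in within-person SD units of the score used (weekly or daily). A given change in servings is therefore a different d on the two scales.
- Small to medium, the article's expectation for the index, is taken as d = 0.2 to 0.5, with d = 1.0 for sensitivity.
- The shift is the same in every participant, and items are otherwise independent.
- An edge is tested at 5%. This is a yardstick; the article states no edge test.

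**Step 1: variance left by the phase pattern f over 15 weeks.**
- Sustained step (0, 1, 1): V = (2/15)(13/15) = 0.116.
- Step that reverts at follow-up (0, 1, 0): V = (7/15)(8/15) = 0.249.
- A step in each phase (−1, 0, +1): V = 8/15 − (4/15)² = 0.462.

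**Step 2: induced correlation.** For two items that are independent within phase and both shifted by d, r = d²V / (1 + d²V).

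| Pattern | d = 0.2 | d = 0.5 | d = 1.0 |
|---|---|---|---|
| Sustained | 0.005 | 0.028 | 0.104 |
| Reverting | 0.010 | 0.059 | 0.199 |
| Step in each phase | 0.018 | 0.104 | 0.316 |

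The sign is negative if the two items move in opposite directions. In a sample, person-mean centring leaves 14/15 of the residual variance, so the values are slightly higher. For the sustained 1 SD step, 15 × 0.1156 = 1.73 and r = 1.73 / (1.73 + 14) = 0.11. For a step of 1 SD in each phase, r = 6.93 / 20.93 = 0.33.

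**Step 3: partial correlation.** With k items shifted alike, partial r = r / (1 + (k − 2)r). For k = 5:
- Sustained 1 SD step: 0.11 / 1.33 = 0.08.
- Step of 1 SD in each phase: 0.33 / 1.99 = 0.17.

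On 315 weekly rows, |r| of about 0.115 reaches 5%: tanh(1.96/√291) = 0.114.

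**Step 4: false-edge rate by simulation.** The set-up was 12 items, 21 participants, person-mean centring and partial correlations from the inverse covariance. Each range runs from 10 shifted items (lower rate) to 2 (higher rate).

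| Scenario | d = 0.5 | d = 1.0 |
|---|---|---|
| Weekly, sustained | 7–8% | 17–43% |
| Weekly, reverting | 11–17% | 26–97% |
| Weekly, step in each phase | 17–49% | 33–100% |
| Daily, sustained | 18–27% | not run |
| Daily, reverting | 47–81% | not run |

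With no shift the rate is 5.0%. At d = 0.2 on weekly data it stays close to 5%. In a 7-person group the bias is the same, but fewer edges reach significance: for reverting d = 1.0 the rate is 11–53%.

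**Step 5: centring within person and phase.** The mean partial r between shifted items returns to 0.00 and the weekly false-edge rate to about 5% (3.5% to 7.2%, simulation noise). Within-person degrees of freedom fall from 315 − 21 = 294 to 315 − 63 = 252, which is 42 fewer or 14%. On daily data they fall from 2184 to 2142, or 2%.

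**The case against.** Several points against the concern are sound.

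**The objective is wider than spillover.** It also covers covariation occurring over the study, and the pooled network describes total covariation validly. Phase centring has a real loss. Substitution that takes place as a shift between phases (meat down 1 SD, another protein up 1 SD) gives about −0.11 under the planned centring and 0 under phase centring. The article's own examples, meat replaced by cheese or by other animal protein, could well take that form. This stands, and it is why the pooled network should not be replaced or demoted.

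**The size may be small.** Two of the sensitivity patterns, a sustained 1 SD step and a 0.5 SD step in each phase, have the same between-phase variance of 0.116. With five co-shifting items both give partials near 0.08, below the 0.115 yardstick. Tailored feedback and mixed responses also dilute the effect. If each item moves by 1 SD in an independent half of participants, the covariance falls to 0.25 × 0.116 = 0.029, and the partial to about 0.03. This stands too.

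**The stakes are modest.** This is a secondary, visual analysis in a pilot, without specific hypotheses and with no stated edge test. The cited network guidelines are not at hand and may set further rules. This limits the weight of the point, but it does not justify reading an edge as spillover.

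A reader might infer that a successful intervention would necessarily yield a positive network of false spillovers. The documents do not support that. Items are expected to move in both directions, so the induced edges would be mixed in sign. At the small-to-medium shifts the article expects, a sustained change on weekly data adds little.

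**Conclusion.** The point holds as a limit on interpretation. With 12-month centring and pooled phases, an edge between two targeted items may reflect within-phase covariation, a common response to the intervention, or substitution between phases. The pooled network alone cannot tell these apart, so the step from associated deviations to spillover is not warranted.

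The size is uncertain because item SDs are not stated. The false-edge rates rest on the inferred 2/7/6 split, a shift common to all participants and a 5% edge test. On weekly data they run from no material excess at 0.2 SD, through 7–8% for a sustained 0.5 SD step, to large values with 1 SD shifts, reversion or a step in every phase. Daily data raise the rate at a given d. The wish for statistical power is a weak reason to report only the pooled network, since phase centring costs 14% of within-person degrees of freedom on weekly data and 2% on daily data. This is a cheap improvement to a secondary analysis, not a defect in the primary ones.

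**What to change.** 1. Keep the pooled network as planned, and label it as total covariation over the study, including the common response to the intervention.
2. Report beside it a second network in which each item is centred on the participant's mean within each phase, labelled as within-phase covariation.
3. State that an edge between targeted items will not be called spillover from the pooled network alone. An edge that appears only there is compatible with a common intervention response or with phase-level substitution. Read it together with the phase effects of the two items.
4. Phase models are already planned under objective 1.1.b for four food groups and food waste. Where an edge involves another item, such as legumes or white meat, fish and eggs, report that item's phase effect as well.

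**Cost.** One more network per group analysed, a few lines of code, and 42 fewer within-person degrees of freedom in that network for the whole sample. The within-phase network cannot show substitution that occurs as a phase-level shift, which is why both are needed. It also does not remove trends within a phase; a time term would be needed for those.
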